**Figure 1 f1:**
[figure not shown]
Flow diagram of the study patient disposition throughout the trial. AMI, acute myocardial infarction; T2DM, type 2 diabetes mellitus; eGFR, estimated glomerular filtration rate; SGLT2i, sodium-glucose cotransporter-2 inhibitor.

### Endpoints

2.4

The primary endpoint is the change of cardiac function [LV end-systolic volume index (LVESVi)] measured by cardiac magnetic resonance (CMR) in T2DM patients with AMI. The secondary endpoints are (I) other changes in parameters of cardiac function measured by CMR and echocardiography (LVEF, LV mass, LV volume); (II) change in KCCQ-OS and EQ-5D from baseline; (III) change in biomarkers related to myocardial parietal stress [N-terminal fragment brain natriuretic peptide (NT-pro BNP)], myocyte injury (creatine kinase, TnI, TnT), fibrosis (sST2, Gal-3), inflammation including interleukin-1β (IL-1β), interleukin-6 (IL-6), interleukin-8 (IL-8), interleukin-10 (IL-10), tumor necrosis factor-α (TNF-α), procalcitonin (PCT), C-reactive protein (CRP), and FGF21 in hospital laboratory research, as well as miRNA level. The detailed endpoints are provided in **Table 2**.

**Table 2 T2:** Trial endpoints.

	Outcome measures
Primary endpoint	
Cardiac function in T2DM patient with AMI 12 months after the event	Change in LVESVi from baseline to the study end at 12 months measured by cardiac MRI
Secondary endpoints	
1. Parameters of cardiac structure	Change in LVEF, LV mass, LV volume at 3 months, 6 months, and 12 months after hospitalization for new-onset AMI
2. Biomarkers related to myocardial parietal stress 3. Biomarkers related to AMI 4. Biomarkers related to fibrosis 5. Biomarkers related to inflammation	Change in NT-pro BNP; Change in CK, TnI, TnT; Change in sST2, Gal-3; Change in IL-1β, IL-6, IL-8, IL-10, TNF-α, CRP, and PCT; at 3 months, 6 months, and 12 months after hospitalization for new-onset AMI
6. Questionnaire’s instructions on health status	Change in KCCQ-OS and EQ-5D at 3 months, 6 months, and 12 months after hospitalization for new-onset AMI
Exploratory endpoints on the mechanisms	
To investigate that whether SGLT2i will have an effect on miRNAs and FGF21	Change in miRNAs and FGF21

AMI, acute myocardial infarction; LVESVi, LV end-systolic volume index; MRI, magnetic resonance imaging; eGFR, estimated glomerular filtration rate; SGLT2i, sodium-glucose cotransporter-2 inhibitor; LV, left ventricular; EF, ejection fraction; NT-pro BNP, N-terminal fragment brain natriuretic peptides; CK, creatine kinase; TnI, Troponin I; TnT, Troponin T; sST2, soluble suppression of tumorigenicity-2; Gal-3, galectin-3; KCCQ-OS, Kansas City Cardiomyopathy Questionnaire overall summary score; EQ-5D, EuroQol- 5 dimension; FGF21, fibroblast growth factor 21.

### CMR and analysis

2.5

Contrast-enhanced CMR will be performed on a clinical 3.0-Tesla scanner (Achieva TX, Philips Healthcare, Best, Netherlands) within 14 days after the first PCI and at 1-year follow-up. All images will be obtained in breath-hold with a default field of view of 350 × 350 mm^2^. An experienced reader blinded to clinical data will analyze the CMR image with commercially available software (QMassx MR 7.5, Medis Medical Imaging, Leiden, Netherlands). The endocardial contour of the LV will be delineated excluding trabeculations and LV papillary muscles. In cases with significant discrepancy, the contours will be reviewed and corrected by a consensus group. Quantitative detection of LV volume and LVEF will be calculated based on short-axis slices of cine images covering the whole heart at end systole and end diastole, respectively. The extent of both infarction and microvascular obstruction will be semiquantified as a percentage of LV myocardial mass (% LVM).

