#### Inclusion

2.2.1

(I) Men and women aged 18–80 years with T2DM and AMI undergoing successful percutaneous coronary intervention (PCI) within 14 days of hospital admission;

(II) treated with at least one antidiabetic drug besides lifestyle interventions;

(III) estimated glomerular filtration rate (eGFR) ≥45 mL/min/1.73 m^2^;

(IV) diagnosed with either ST-elevation myocardial infarction (STEMI) or non-ST elevation myocardial infarction (NSTEMI) according to the Fourth Universal Definition of Myocardial Infarction (27) and T2DM diagnosed based on the guideline for the prevention and treatment of T2DM in China (2020 edition) (28).

(V) Severe myocardial necrosis with a rise in CK >800 U/L and a TnT level or TnI level >10× upper limit of normal (ULN) after AMI (29, 30).

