### Intervention

2.3

Patients with T2DM will continue the previous glucose-lowering regimen unless glycemic control deteriorates requiring regimen to be adjusted. Patients who received SGLT2i are considered as SGLT2 inhibitors group, and patients not taking any SGLT2i are considered as non-SGLT2 inhibitors group (control group). Based on the requirement of open-label study, patients will be assigned to a 1-year treatment with either SGLT2i (empagliflozin 10 mg/day or dapagliflozin 10 mg/day or canagliflozin 100 mg/day) or other antidiabetic drugs [insulin, metformin, α-glucosidase inhibitors, sulfonylurea hypoglycemic agents, dipeptidyl peptidase-4 inhibitors (DPP4i), glucagon-like peptide-1 (GLP1) receptor agonists, and so on] (31). Patients without SGLT2i contraindication were prescribed one type of SGLT2i, other patients used other antidiabetic drugs in order to maintain the blood glucose into the target in the hospitalization (fasting blood glucose 7.8–10 mmol/L, postprandial blood glucose 7.8–13.9 mmol/L) (31). Considering the beneficial effects on LV function and high availability in China (26), empagliflozin was recommended first. Participants with contraindications of SGLT2i including those with the presence of ketone bodies or genitourinary infections might be assigned to the control group without SGLT2i. Of note, DPP4i (saxagliptin or sitagliptin) and thiazolidinediones (such as rosiglitazone or pioglitazone) are not preferred in patients with AMI combined with HF, which may worsen HF and cause hospitalization based on the present guideline (32).

Patients will participate in three visits (at 3, 6, and 12 months after hospitalization for new-onset AMI) in 1 year (see **Figure 1** for an overview of all visits’ process).

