#### Blood samples

2.7.1

Blood samples for routine biomarkers (NT-pro BNP, creatine kinase, TnI, TnT, sST2, IL-1β, IL-6, IL-8, IL-10, TNF-α, CRP, PCT, Gal-3) will be collected and measured by the hospital laboratory service from the eligible patients within 14 days after AMI incidence and at 1-year follow-up. A total of approximately 8 mL of blood samples will be drawn from the antecubital vein into two vacuum blood collection tubes at two time points: on the first 14 days of AMI (admission) and at 1 year following AMI. To obtain plasma, 4 mL of blood sample with anticoagulants (EDTA) will be centrifuged at 3,000 rpm for 10 min at 4°C, then the yellow cell-free supernatant will be collected and frozen in RNase-free Cryo-Tubes under -80°C until further processing. To obtain serum, the tubes without anticoagulants within 4 mL of peripheral blood samples are let stand at a 45- to 60-degree angle under 4°C for at least 1 h to promote coagulation. Then, the blood is centrifuged within 10 min of withdrawal at 3,000 rpm for 10 min to obtain the serum, which will be separated into RNase-free tubes. The handled samples are stored under -80°C to be used further for the miRNAs and FGF21 detector.

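### Baseline is not tied to first SGLT2i exposure, so change in LVESVi can miss part of any drug effect and mixes continued use with new starts; for CK and troponin, change largely reflects sampling day and infarct size.

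*Protocol article*

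**What the plan says.** Exposure (Protocol article, 2.3 Intervention). The section opens with continuity of treatment: "Patients with T2DM will continue the previous glucose-lowering regimen unless glycemic control deteriorates requiring regimen to be adjusted". It then defines the groups: "Patients who received SGLT2i are considered as SGLT2 inhibitors group", and those not taking any such drug are controls. The same section speaks of assignment to one year of treatment and of prescribing an SGLT2i in hospital to patients without a contraindication. The criteria in 2.2.1, 2.2.2 and Table 1 do not exclude prior SGLT2i use.

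Baseline (2.5 and 2.7.1). CMR is done "within 14 days after the first PCI and at 1-year follow-up". Routine biomarkers are drawn "within 14 days after AMI incidence and at 1-year follow-up", and the same section later words this as "on the first 14 days of AMI (admission) and at 1 year following AMI". Entry requires AMI "undergoing successful percutaneous coronary intervention (PCI) within 14 days of hospital admission" (2.2.1), so PCI has a window of its own.

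Endpoints (2.4 and Table 2). The primary endpoint is change in LVESVi from baseline to 12 months. Change in CK, TnI and TnT is secondary. Entry requires "Severe myocardial necrosis with a rise in CK >800 U/L" together with troponin above ten times the upper limit of normal (2.2.1).

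Aim (3 Discussion). The stated interest is in early initiation of SGLT2i after AMI.

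**The concern.** A change score estimates the effect of starting a drug only if its baseline precedes the drug. Here two kinds of patient can enter the SGLT2i group with a baseline that does not. A prior user is on drug at the baseline scan by definition. An in-hospital starter may be scanned, or bled, after the first dose, because nothing in 2.3, 2.5 or 2.7.1 orders these events. The primary contrast then averages over continued use and new use, and can miss whatever effect came before the scan.

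Prior use is plausible. Entry requires at least one antidiabetic drug, and the Introduction says that guidelines strongly recommend SGLT2i in patients with T2DM and CVD.

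CK and troponin raise a separate problem. Every patient starts from a large acute rise, sampled on any day of a 14-day window. The 12-month change is then governed mostly by how large the infarct was and when the tube was filled, and little by what treatment did over the year.

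**Working it through.** **1. The plan's own sample size.** Inputs from 2.8.1: changes of -7.9 and -1.5 mL/m², so the difference is 7.9 - 1.5 = 6.4; SDs 11.8 and 11.3; power 80%; α = 0.025; dropout 10%. With SD 11.8 and one-sided 0.025 (equivalent to two-sided 0.05):

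n per arm = 2 × (1.960 + 0.842)² × 11.8² / 6.4² = 53.4, rounded up to 54. Total 108; 108 / 0.9 = 120.

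The stated 108 and 120 are reproduced. Power at 54 per arm is Φ(6.4 / (11.8 × √(2/54)) - 1.960) = Φ(0.858) = 80.5%. There is almost no slack, and the calculation assumes that the whole 6.4 mL/m² arises between baseline and follow-up.

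**2. If a fraction f of the difference is lost because exposure began before baseline.** The documents give no value for f; it is an assumption. Power = Φ(6.4 × (1 - f) / (11.8 × √(2/54)) - 1.960).

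| f (assumed) | Difference (mL/m²) | Power, 54 per arm | Evaluable N for 80% |
|---|---|---|---|
| 0 | 6.40 | 80.5% | 108 |
| 5% | 6.08 | 76.3% | 120 |
| 10% | 5.76 | 71.8% | 132 |

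**3. The floating CMR window alone.** If scan day is uniform over 0 to 14 days in both groups, its SD is 14/√12 = 4.04 days. With an assumed drift of b mL/m² per day, the SD becomes √(11.8² + (4.04b)²).

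| b (assumed) | SD | Power |
|---|---|---|
| 0.25 | 11.84 | 80.2% |
| 0.5 | 11.97 | 79.3% |
| 1 | 12.47 | 76.0% |

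Window noise by itself costs little. Exposure before baseline is the main issue for LVESVi.

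**4. Time anchors.** Taken at both literal limits, PCI on day 14 after admission and CMR 14 days after PCI put the baseline scan at 14 + 14 = 28 days after admission. Baseline blood must be drawn within 14 days of AMI, and is once glossed as admission. The 28 days is a worst case, not an expected timing, but it shows that the two baselines need not describe the same moment.

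**5. CK and troponin.** Assume a first-order fall with a half-life of 1 to 3 days (an assumption, not a figure in the documents). A 2-day difference in sampling multiplies the baseline by 2^(2/3) = 1.6 to 2^(2/1) = 4. The 12-month value cannot offset this, so the spread passes directly into the change score.

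**The case against.** Several points on the other side stand.

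- A reader might infer immortal-time bias from a group defined by having received the drug. This does not fit: the primary outcome is a 12-month CMR change, which patients in both groups must survive to provide, and no person-time is being allocated. The text in 2.3 on assignment to one year of treatment also points to grouping at the index admission. What is missing is an explicit statement of that.
- A reader might infer that the result must be pulled towards zero, or might quantify the dilution by guessing the share of prior users and assuming no further drug effect in them. The documents support neither. Remodelling after the infarct also takes place on drug in a prior user who continues, and in a non-randomised comparison prior users may differ in other ways, so the direction is open.
- A few days of dosing before the scan matter only if LVESVi responds that quickly, and the documents give no early effect.
- A reader might conclude that the CK and troponin endpoints cannot show any 12-month drug effect, or compare one patient sampled at the peak with one sampled after recovery. Both go too far. If sampling day is alike in the two groups it adds noise, not a false difference, and these endpoints are secondary.
- The patient-flow figure is not shown and may give an order of events. A journal article may also leave case-report-form details to the full protocol.

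These points limit the claim but do not remove it. The article itself sets the windows, the group definition and the endpoints, and as written they allow on-drug baselines in a study of early initiation.

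**Conclusion.** The concern holds in limited form. Baseline is not tied to first exposure, prior users are neither excluded nor separated, and the CMR and blood baselines have different anchors that overlap with in-hospital prescribing. The primary change score can therefore miss part of any drug effect, and it mixes continued use with initiation. How far and in which direction this moves the result cannot be derived from the documents. The fall in power to 76.3% or 71.8% is an illustration that rests on an assumed loss of 5% or 10%; its firm content is only that a design at 80.5% has no margin for such a loss.

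Change in CK, TnI and TnT is a weak endpoint because it largely reflects sampling day and infarct size. It becomes biased only if sampling day differs by group. That is possible because group depends partly on contraindications such as ketone bodies or genitourinary infection (2.3), but nothing shown says that it happens. The regression described in 2.8.2 names no timing variable.

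**What to change.** - Record the dates of AMI, PCI, baseline CMR, baseline blood draw and first SGLT2i dose.
- State that group is fixed at the index admission.
- Make patients with no SGLT2i use before that admission the primary analysis set, or at least a pre-specified key sensitivity analysis. Report prior users separately.
- Adjust the LVESVi comparison for days from PCI to baseline CMR, and add a sensitivity analysis limited to scans made before the first dose.
- Replace change in CK, TnI and TnT by the log 12-month level, and use the acute values only as a covariate for infarct size.
- Reconcile the time anchors in 2.2.1, 2.5 and 2.7.1, including the two wordings of the blood window, and their order relative to the exposure definition in 2.3. This concerns the definition of baseline and does not call for a change in when treatment starts.

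The cost is five dates on the case report form and some analysis wording. The downside is a somewhat smaller primary set if prior users are removed. The documents do not say how many that would be, and with 53.4 per arm needed against 54 planned there is no spare precision, so the number of prior users should be monitored during recruitment.

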### Questionnaire’s instructions

2.6

KCCQ-OS is designed for patients with HF to evaluate the frequency of HF symptom, physical limitation, quality of life, and social limitation (33, 34). EQ-5D is an instrument to evaluate the quality of life in terms of five dimensions including mobility, self-care, activities, anxiety/depression, and pain/discomfort (35). Both full scores are ranging from 0 to 100, with higher scores reflecting better health status. The KCCQ and EQ-5D questionnaires are documented in **Supplementary Table S1** and **Supplementary Table S2**, respectively.

### Biomarkers of cardiac function

2.7

#### Blood samples

2.7.1

Blood samples for routine biomarkers (NT-pro BNP, creatine kinase, TnI, TnT, sST2, IL-1β, IL-6, IL-8, IL-10, TNF-α, CRP, PCT, Gal-3) will be collected and measured by the hospital laboratory service from the eligible patients within 14 days after AMI incidence and at 1-year follow-up. A total of approximately 8 mL of blood samples will be drawn from the antecubital vein into two vacuum blood collection tubes at two time points: on the first 14 days of AMI (admission) and at 1 year following AMI. To obtain plasma, 4 mL of blood sample with anticoagulants (EDTA) will be centrifuged at 3,000 rpm for 10 min at 4°C, then the yellow cell-free supernatant will be collected and frozen in RNase-free Cryo-Tubes under -80°C until further processing. To obtain serum, the tubes without anticoagulants within 4 mL of peripheral blood samples are let stand at a 45- to 60-degree angle under 4°C for at least 1 h to promote coagulation. Then, the blood is centrifuged within 10 min of withdrawal at 3,000 rpm for 10 min to obtain the serum, which will be separated into RNase-free tubes. The handled samples are stored under -80°C to be used further for the miRNAs and FGF21 detector.

#### Analysis of FGF21

2.7.2

The concentration of serum FGF21 is measured by a commercially quantitative human ELISA kit (DF2100, R&D Systems, Minneapolis, MN, USA) according to the manufacturer’s instructions. Absorbance at 450 nm is performed using a microplate reader (BioTek, Winooski, VT, USA). According to the manufacturer’s information, the inter-assay and intra-assay coefficients of variation were 2.9%–3.9% and 5.2%–10.9%, respectively.

#### Analysis of miRNA

2.7.3

Total RNA is extracted from the handled serum *via* standard procedures using DNase I RNase-free (Takara) to remove genomic DNA according to the manufacturer’s instruction (Invitrogen). The purity and concentration of our RNA are measured using ND-2000 (NanoDrop Technologies). RNA integrity is evaluated by 2100 Bioanalyzer (Agilent Technologies, Santa Clara, CA, USA). First-strand cDNA is synthesized using M-MuLV Reverse Transcriptase (RNase H–). Amplification and detection by polymerase chain reaction (PCR) are performed using LongAmp Taq 2X Master Mix, SR Primer. The expression of miRNA is assessed by quantitative real-time PCR and calculated according to the transcripts per million reads (TPM) method. Significant differently expressed (DE) miRNAs are extracted with |log2 fold change (FC)| >1 and False Discovery Rate (FDR) <0.05 by DEseq2.

### Study statistics

2.8

#### Sample size calculation

2.8.1

The sample size of this trial is calculated based on the primary outcome—the change in LVESVi. In a recent randomized controlled trial (SUGAR-DM-HF), the mean ± standard deviation (SD) of change in LVESVi in the experimental group and control group was -7.9 ± 11.8 mL/m^2^ and -1.5 ± 11.3 mL/m^2^, respectively (24). These data were for an 80% power at a 2.5% significance level [α = 0.025] with a 1% margin of error. Sample size was calculated to be 108 patients randomly assigned 1:1 to empagliflozin 10 mg once daily or placebo (24). Considering a 10% dropout in our previous study due to the presence of dressing change or medication nonadherence, a sample size of 120 subjects (two groups of 60) is necessary.

#### Statistical analysis

2.8.2

Continuous variables will be described as mean with SD and compared by unpaired Student’s t-tests or Mann–Whitney U tests. Categorical variables of baseline characteristics will be summarized using count statistics, presented as percentage n (%) as appropriate. Chi-square test will be used when sample size is larger than 40; Fisher’s exact test will be used when sample size is smaller than 40. The results with p values <0.1 in univariate regression or considered meaningful in clinical practice will be further analyzed using multivariate regression to explore the effects of SGLT2i on LV function. All analyses will be conducted using the SPSS software, version 22.0 (SPSS Inc., Chicago, IL, USA).

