However, it is important to acknowledge certain limitations of this study. This trial is a parallel group and single-center research that recruits patients with T2DM and severe AMI with complex conditions such as HF or CKD. Thus, whether these findings can speculate to other more uncomplicated patients needs to be further studied. To enhance the credibility of the results, the study employs univariate and multivariate analyses to migrate the possible influences.

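### The only stated group comparison for the LVESVi change is unadjusted although the groups are not randomised; the adjusted regression is exploratory, screened by p<0.1 and not fixed as primary

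*Protocol article*

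**What the plan says.** - **Endpoint.** Section 2.4, Table 2 defines the primary outcome as "Change in LVESVi from baseline to the study end at 12 months measured by cardiac MRI".
- **Stated comparison.** Section 2.8.2: "Continuous variables will be described as mean with SD and compared by unpaired" t-tests or Mann–Whitney U tests. The sentence is generic and does not name LVESVi, but no other group test is given for a continuous outcome. The sample size in section 2.8.1 is also built on two mean changes and their SDs, without covariates.
- **How groups arise.** Section 2.3: "Patients who received SGLT2i are considered as SGLT2 inhibitors group", and "Patients without SGLT2i contraindication were prescribed one type of SGLT2i, other patients used other antidiabetic drugs". No randomisation procedure is described for this study. The reference to 1:1 random assignment in section 2.8.1 is to empagliflozin or placebo, as in the cited trial, and this study has no placebo arm.
- **Stated adjustment.** Section 2.8.2 sends variables with p<0.1 in univariate regression, or those "considered meaningful in clinical practice will be further analyzed using multivariate regression to explore the effects of SGLT2i on LV function". The Discussion's limitations paragraph relies on this: "the study employs univariate and multivariate analyses to migrate the possible influences".
- **Data available.** Section 2.5 schedules CMR "within 14 days after the first PCI and at 1-year follow-up", so baseline LVESVi is measured. It adds: "The extent of both infarction and microvascular obstruction will be semiquantified as a percentage of LV myocardial mass".

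**The concern.** An unpaired test of change is a sound primary comparison when randomisation makes the groups alike at baseline. Here treatment depends on contraindication and prescribing, so baseline LV volume and other prognostic factors can be expected to differ. A patient who starts with a larger LVESVi tends to show a larger fall whatever the treatment, and the unpaired test credits that fall to the group.

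The planned regression does not settle this. Its covariates depend on the data or on a later judgement, so an important confounder can miss the p<0.1 cut-off in a study of 120. Baseline LVESVi may or may not enter. With an unadjusted and an adjusted answer both available and neither ranked, the headline result could be chosen after the data are seen. The sole primary estimate is at stake.

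**Working it through.** **Inputs from section 2.8.1.** Mean changes −7.9 (SD 11.8) and −1.5 (SD 11.3) mL/m²; difference 6.4; power 80%; α 0.025; 108 evaluable, 120 enrolled. Pooled SD = √[(11.8² + 11.3²)/2] = 11.55.

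**Step 1: reproduce the plan's figure.** Per-arm n = 2(z_α + z_β)² SD²/Δ².
- One-sided 0.025 (1.96 + 0.842) with SD 11.55: 52 per arm, 104 in total. The t-test version gives 106.
- The same with the larger SD of 11.8: 54 per arm, 108 in total.
- Dropout: 108/(1 − 0.10) = 120.
- Two-sided 0.025 gives 124 (normal) or 128 (t), which does not reproduce 108.

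The planned size is therefore that of an unadjusted two-mean comparison, which supports reading the unpaired test as the planned primary comparison.

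**Step 2: what a baseline gap does.** The article gives no correlation ρ between baseline and 12-month LVESVi, so ρ = 0.5 to 0.9 is assumed, with equal SDs at both times. If both groups would regress to a common mean without a drug effect, the shift in the difference in change is (1 − ρ) × gap. For an assumed gap of 5 mL/m²:
- ρ 0.5: 2.5 mL/m², 2.5/6.4 = 39%
- ρ 0.7: 1.5 mL/m², 1.5/6.4 = 23%
- ρ 0.9: 0.5 mL/m², 0.5/6.4 = 8%

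The standard error at 54 per arm is 11.55 × √(2/54) = 2.22, so these shifts are about 1.1, 0.7 and 0.2 standard errors. The sign depends on which group starts higher.

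**Step 3: precision.** Var(ANCOVA)/Var(change) = (1 − ρ²)/[2(1 − ρ)] = (1 + ρ)/2, which is 0.75, 0.85 and 0.95 at ρ 0.5, 0.7 and 0.9. At 54 per arm and two-sided 0.05, power is 82.1% unadjusted and 91.4%, 87.7% and 84.0% with ANCOVA.

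**Step 4: loss from imbalance.** A baseline gap of D within-group SDs multiplies the ANCOVA variance by about 1 + D²/4. At D = 0.5 the factor is 1.0625. The net ratio is 0.85 × 1.0625 = 0.90 at ρ 0.7, and 0.95 × 1.0625 = 1.01 at ρ 0.9, where the gain is gone.

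**The case against.** **Adjustment is already planned.** This stands in part. A reader might infer from the t-test sentence that the plan is wholly unadjusted, or that baseline LVESVi is excluded. Sections 2.8.2 and 3 do not support that: there is a multivariable regression, and baseline LVESVi or infarct size could enter by either route. The defect is that this analysis is exploratory, selected from the data, and not primary.

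**The covariate list belongs in the SAP.** The SAP is not shown, and a missing list would be no finding. The point rests on what the article does state: the test, the p<0.1 rule and the exploratory role.

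**Bias is not certain.** This stands. The formula in step 2 needs regression to a common mean. If the groups have stably different means with parallel trends, the change score is unbiased and ANCOVA is off by the same (1 − ρ) × gap (Lord's paradox).

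**The error rate cannot be stated.** A reader might infer a grossly inflated type I error. A value near 34% follows if five factors are each imbalanced by 0.3 SD in the same direction with outcome slope 0.2: bias 5 × 0.3 × 0.2 = 0.30 SD, standard error √(2/54) = 0.19 SD. With three factors one way and two the other, bias is 0.06 SD and the rate about 6%. None of these inputs is in the article, so no such rate can be claimed.

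**Some proposed covariates may be post-treatment.** This stands. SGLT2i may be continued from before admission or given in hospital, while baseline CMR may come up to 14 days after PCI. Infarct size and microvascular obstruction may therefore already reflect treatment, and forcing them in could remove part of the effect. Baseline LVESVi shares this weakness, but so does the change score, which subtracts the same scan.

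**Conclusion.** The point holds in this form: in a non-randomised comparison, the only stated group test for the LVESVi change is unadjusted, and the analysis meant to handle confounding is neither fixed in advance nor designated primary. Applying the generic test sentence to LVESVi is an inference, but a well-supported one.

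The size is illustrative. A shift of 2.5 to 0.5 mL/m² (39% to 8% of 6.4) rests on an assumed 5 mL/m² gap, an assumed ρ of 0.5 to 0.9, and regression to a common mean. The documents support neither a claim that the estimate will be biased in a known direction nor a particular false-positive rate. Lower variance with baseline adjustment is usual but not guaranteed.

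**What to change.** In section 2.8.2, name one primary analysis: a linear model of 12-month LVESVi on group, baseline LVESVi and a fixed, pre-specified list of pre-treatment confounders, for example STEMI/NSTEMI, age, sex, eGFR and days from PCI to baseline CMR. Using the change as outcome gives the same group coefficient once baseline LVESVi is in the model. Report the adjusted difference with its 95% CI. Drop the p<0.1 screen and label the unpaired test descriptive.

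Add infarct size and microvascular obstruction in a sensitivity analysis only, and record when SGLT2i was started relative to the baseline CMR so that it can be interpreted.

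The cost is wording: baseline CMR is already scheduled, and the other listed covariates are eligibility items, basic demographics or dates. The downside is small. Adjustment does not remove unmeasured confounding, and the precision gain can vanish with high correlation and marked imbalance.

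### KCCQ-OS and EQ-5D are measured at three follow-up visits in non-randomised groups, but the only comparison named for them is an unadjusted two-sample test, with no main time point

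*Protocol article*

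**What the plan says.** Section 2.8.2 (Statistical analysis) gives one rule for continuous outcomes: "Continuous variables will be described as mean with SD and compared by unpaired" t-tests or Mann–Whitney tests. The only other between-group analysis takes results that pass a univariate screen (p below 0.1) or are judged clinically meaningful, to be "further analyzed using multivariate regression to explore the effects of SGLT2i on LV function". No repeated-measures method is named, and no significance level is given for secondary endpoints.

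Section 2.3 (Intervention) sets the follow-up: "Patients will participate in three visits (at 3, 6, and 12 months after hospitalization for new-onset AMI) in 1 year". Table 2 in Section 2.4 (Endpoints) attaches those times to the questionnaires, "Change in KCCQ-OS and EQ-5D at 3 months, 6 months, and 12 months after hospitalization for new-onset AMI", and to the LV parameters, "Change in LVEF, LV mass, LV volume at 3 months, 6 months, and 12 months after hospitalization for new-onset AMI". It gives the routine biomarkers the same three times.

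The methods text differs. Section 2.5 schedules CMR "within 14 days after the first PCI and at 1-year follow-up". Section 2.7.1 takes routine biomarker blood "from the eligible patients within 14 days after AMI incidence and at 1-year follow-up" and describes the draws as "at two time points: on the first 14 days of AMI (admission) and at 1 year following AMI".

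Group membership depends on treatment. Section 2.3 gives an SGLT2 inhibitor to patients without a contraindication, and patients with one may go to the control group.

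**The concern.** A two-sample test uses one value per patient. KCCQ-OS and EQ-5D have three follow-up values each, and the article names neither a main visit nor a summary value, so the test has no single defined input. Two consequences follow.

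- **Confounding.** Patients with and without a contraindication to SGLT2 inhibitors may well differ at baseline. An unpaired test of change makes no allowance for that. LV function has a regression that can make one; the questionnaires, as written, do not.
- **Several answers per endpoint.** Three visit-wise tests give three chances of a significant result and no agreed one to report. Each test also uses only patients seen at that visit, and Section 2.8.1 expects 10% dropout.

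The Discussion lists the quality-of-life assessment among the study's main strengths, so its analysis should give one interpretable answer.

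**Working it through.** **1. Which endpoints can have three follow-up values**

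| Endpoint | Table 2 | Methods text |
|---|---|---|
| KCCQ-OS, EQ-5D | 3, 6, 12 months | three visits (2.3), no conflict |
| LV parameters by CMR | 3, 6, 12 months | baseline and 1 year (2.5) |
| LV parameters by echocardiography | 3, 6, 12 months | no schedule given |
| Routine biomarkers | 3, 6, 12 months | baseline and 1 year (2.7.1) |

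Only the questionnaires clearly qualify. Echocardiographic measures qualify if taken at each visit.

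**2. The plan's own figure and the significance level behind it**

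Section 2.8.1 gives changes of −7.9 and −1.5 mL/m² (difference 6.4), SDs 11.8 and 11.3, 80% power and α = 0.025 with sidedness unstated. Per group, n = 2(z_α + z_β)²·SD²/difference².

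- One-sided 0.025 (equivalent to two-sided 0.05), SD 11.8: 2 × (1.960 + 0.842)² × 139.24/40.96 = 53.4, so 54 per group, 108 in total; 108/0.9 = 120. This matches the article.
- Two-sided 0.025, SD 11.8: 64.6, so 65 per group, 130 in total. This does not match.

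The article's number therefore fits two-sided 0.05, but that level is never stated for secondary endpoints, so both levels are carried below.

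**3. Chance of at least one false positive over three visits, no true effect**

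With equal variances and a common correlation ρ between all visits, two changes from the same baseline have covariance (1 − ρ)σ² and variance 2(1 − ρ)σ². They correlate 0.5 whatever ρ is. Independent tests would give 1 − 0.95³ = 14.3%. The correlated cases were simulated with at least two million draws:

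| Correlation between tests | Two-sided 0.05 each | Two-sided 0.025 each |
|---|---|---|
| 0 | 14.3% | 7.3% |
| 0.4 | 13.1% | 6.8% |
| 0.5 | 12.5% | 6.5% |
| 0.6 | 11.8% | 6.2% |
| 0.8 | 9.8% | 5.1% |
| 0.9 | 8.3% | 4.4% |

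An endpoint with one follow-up value has one test and no inflation across visits.

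**4. What baseline adjustment gains at 12 months**

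Assumed, not in the article: 54 per group, true difference 0.4 SD, two-sided 0.05, ρ = 0.4–0.6, similar baseline distributions in the groups, complete data. Outcome variance in units of σ² is 2(1 − ρ) for a change score and 1 − ρ² for analysis of covariance (ANCOVA). The noncentrality is 0.4/√(variance × 2/54).

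| ρ | Change-score variance | Power | ANCOVA variance | Power |
|---|---|---|---|---|
| 0.4 | 1.20 | 47% | 0.84 | 61% |
| 0.5 | 1.00 | 54% | 0.75 | 66% |
| 0.6 | 0.80 | 63% | 0.64 | 73% |

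A 3,000-replicate simulation gave 45–62% and 60–72%, within two points of these.

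**The case against.** The strongest reply is that the article never says a test is done at each visit. The sentence on continuous variables is general, the next concerns baseline characteristics, and a condensed article may leave the longitudinal model, the main contrast and multiplicity to a fuller document. It stands that visit-wise testing is an inference. But the article does not defer the method: it names one, and for the questionnaires nothing else is named.

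A reader might infer more than the text supports:

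- *Every secondary endpoint is compared unadjusted.* LV function has a planned multivariate regression, and baseline could enter it.
- *Every secondary endpoint carries a 12–13% false-positive risk.* CMR and biomarker endpoints have one follow-up value under Sections 2.5 and 2.7.1. The figure also needs two-sided 0.05 and a correlation near 0.5, and the article gives neither.
- *Separate tests simply waste the repeated data.* With complete data, an unstructured repeated-measures model without baseline adjustment gives the same visit-wise contrasts. The gain comes from baseline adjustment, from the partial data of patients who miss a visit, and from naming one contrast.
- *A longitudinal model would lift power to about 90%.* A baseline-adjusted average over three visits does reach 86–91% under these assumptions, but it is a different estimand and needs the full effect from month 3 onward.

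The endpoints are also secondary, which limits the weight of the point.

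**Conclusion.** The point holds for KCCQ-OS and EQ-5D. Their only stated group comparison is an unadjusted two-sample test in groups not formed by randomisation, and no main time point is named. It extends to echocardiographic LV measures only in respect of the missing main time point, and only if they are taken at each visit.

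On the natural reading of three tests, the chance of at least one false positive per endpoint is about 12% at two-sided 0.05. The range is 8–14% across correlations, or 4–7% at two-sided 0.025. The gain at 12 months is from about 47–63% to 61–73% power under the assumptions above. It would be smaller if the groups differ much at baseline or if confounders are strongly related to treatment.

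The change is worth making but does not threaten the main result: 12-month LVESVi has one follow-up value and is not affected.

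**What to change.** 1. Reconcile Table 2 with Sections 2.5 and 2.7.1, so that each endpoint has one set of measurement times, and state when echocardiography is done.
2. For endpoints with values at 3, 6 and 12 months, replace the unpaired tests with one mixed model for repeated measures: baseline value, group, visit, group-by-visit and the planned confounders, with unstructured within-patient covariance. This uses partial data from patients who miss a visit, on a missing-at-random assumption. It adjusts only for confounders that are measured.
3. Name one contrast per endpoint in advance, for example the 12-month difference, and report the other visits as estimates with confidence intervals. Naming the contrast, not the model, returns the across-visit false-positive rate to the nominal level.
4. For endpoints with one follow-up value, a baseline-adjusted regression is enough.

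The cost is a paragraph of text and slightly more analysis work, with no new data for the questionnaires. The small downside is that one contrast must be chosen before the results are seen.
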